**Methods:**

We will conduct a 12-week, double-blind placebo-controlled RCT of atorvastatin for lithium-induced NDI at McGill University, Montreal, Canada. We will recruit 60 current lithium users, aged 18–85, who have indicators of NDI, which we defined as urine osmolality (UOsm) < 600 mOsm/kg after 10-h fluid restriction. We will randomize patients to atorvastatin (20 mg/day) or placebo for 12 weeks. We will examine whether this improves measures of NDI: UOsm and aquaporin (AQP2) excretion at 12-week follow-up, adjusted for baseline.

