## Methods

### Study design and study sample

This is a double-blind, placebo-controlled RCT examining the effectiveness of atorvastatin versus placebo in the treatment of lithium-induced NDI. The study will take place at three tertiary care mental health sites in Montreal, Canada: Douglas Mental Health University Institute (DMHUI), Jewish General Hospital (JGH) and McGill University Health Centre (MUHC).

The study will involve treatment with atorvastatin (20 mg/day) or placebo over a period of 12 weeks. We are aiming to recruit sixty individuals between the ages of 18 and 85 with any psychiatric diagnosis who are currently taking lithium for at least 2 months and have a urine osmolality < 600 mOsm/kg after 10-h water restriction. We opted for a urinary osmolality of < 600 mOsm/Kg: patients with < 600 mOsm/kg are at risk of future NDI-related complications, such as CKD and they constitute a large percentage of lithium users (50% of patients). Other studies have used similar, if not less conservative definitions for NDI [25], which are nonetheless of clinical importance and utility [15]. Other authors have used similar or more liberal definitions in NDI treatment studies [25].

The full inclusion and exclusion criteria can be found in Table 1.

**Table 1 Tab1:** Inclusion and exclusion criteria

Inclusion Criteria	Exclusion Criteria
Between ages 18–85	Already taking statins (at least 6 weeks prior to screening)
Bipolar Diagnosis in any phase of illness: euthymic, depressed or hypomanic. Any schizoaffective diagnosis.	History of adverse reaction to statins; allergy to statins
Diagnosed with NDI, defined by routine 10 h water restriction urine osmolality < 600 mOsm/Kg	Contraindications to statin use: pregnancy or lactation, use of fibrates and heavy alcohol use
Currently taking lithium medication (at least 2 months)	Inability to give consent or deemed to have moderate-severe cognitive disturbances by treating clinician
Able and willing to give informed consent	Active liver disease
	Baseline LDL level < 1.5

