### Overview of study procedures

In this double-blind RCT, sixty patients will receive 12 weeks of either treatment (20 mg/day atorvastatin) or placebo. The study will require three visits at baseline, 4-week and 12-week follow-up, for which participants will be compensated. During each visit, blood and urine samples after 10 h of water restriction and 12 h of fasting will be requested. In addition to the primary and secondary outcomes, patients will be monitored for safety using blood tests for liver function (AST and ALT), cholesterol (e.g. low-density lipoprotein (LDL)) and lithium toxicity (lithium levels, estimated glomerular filtration rate (eGFR)). Patients will also complete questionnaires about their medical history and mental health. Mood assessments for depression and mania symptoms will be completed at baseline, 4-week and 12-week follow-up, including the Montgomery-Asberg Depression Rating Scale (MADRS) [26], Young Mania Rating Scale (YMRS) [27], and the Quick Inventory of Depressive Symptoms, Self-report-16 (QIDS-16) [28], Altman Self-Rating Mania Scale (ASMRS) [29].

The primary outcome is change in 10 h water restriction urine osmolality (mOsm/kg) and will be assessed at baseline, 4-week and 12-week follow-up visits (Table 2).

**Table 2 Tab2:** Baseline and follow-up visits schedule of events and assessments

Assessment	Screen	Baseline	4-week	12-week
Blood	√	√	√	√
Urine osmolality	√	√	√	√
Medical History	√	√		√
Mood Assessment		√	√	√
1.MADRS		√	√	√
2.YMRS		√	√	√
3. QIDS		√	√	√
4. Altman self-rating mania scale		√	√	√

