### Assessments

#### Outcomes measures

Our primary outcome will be urinary osmolality after 10-h water restriction. This short-period water restriction was selected given that longer periods of water restriction are often poorly tolerated by patients, especially those on lithium treatment [30]. Clinically, the 10-h water restriction assessment of urine osmolality is often used and is highly specific and sensitive for NDI [25, 31, 32]. We will assess the raw urine osmolality value at 12-weeks, adjusted for baseline. An increase in urine osmolality (mOsm/Kg) values adjusted for baseline will be indicative of improvements in the kidney’s ability to concentrate urine [33, 34]. We hypothesize that higher osmolality values will be observed compared to baseline in patients randomized to atorvastatin.

We chose measures of aquaporin 2 excretion and self-reports of daily fluid intake as the secondary outcomes. Aquaporins are channels involved in water reabsorption in the collecting ducts of the kidney [35]. Assessment of aquaporin excretion in urine will be indicative of the expression of the aquaporin channels and water reabsorption capabilities of the kidneys, allowing further confirmation of whether: 1) NDI pathology is present and 2) whether it is being modified by atorvastatin treatment. Furthermore, changes in daily fluid intake have been highly correlated with both urinary osmolality and the gold-stand as a characteristic of NDI [30, 31, 36]. Additionally, we supplement these secondary measures with self-reported frequency of nighttime and daytime polyuria.

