#### Planned analysis

We will use independent two-tailed Student’s t-test (or non-parametric equivalent) to compare the primary outcome (raw score values of urinary osmolality at 12-weeks, adjusted for baseline) and secondary outcomes (self-reported fluid intake and variation in aquaporin 2 protein abundance in urinary exosomes at 12-week follow-up, adjusted for baseline) between the treatment (atorvastatin) and control (placebo) groups. The consensus in the statistics RCT literature is that clinical trial outcomes should not be “change from baseline”, but rather the raw score of an outcome, adjusted for the baseline value [37]. Randomization is expected to balance potential confounders between the treatment and placebo groups since both groups are anticipated to have roughly equal baseline characteristics, which we will assess using t-tests (or non-parametric equivalent) and chi-squared tests, as appropriate. However, in the event that any important baseline characteristic differs between groups, we will use multiple linear regression to control for that particular characteristic.

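### The primary outcome is given both as change and as the 12-week value adjusted for baseline, and the hypothesis is a within-arm rise that the planned between-arm test does not address

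*Protocol article*

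**What the plan says.** All places are in the protocol article.

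- **Overview of study procedures:** "The primary outcome is change in 10 h water restriction urine osmolality (mOsm/kg"). The same sentence has it assessed at baseline, week 4 and week 12.
- **Outcomes measures:** "We will assess the raw urine osmolality value at 12-weeks, adjusted for baseline".
- **Abstract, Methods:** the measures are "UOsm and aquaporin (AQP2) excretion at 12-week follow-up, adjusted for baseline".
- **Planned analysis:** a two-tailed Student's t-test, or a non-parametric equivalent, of the 12-week value "between the treatment (atorvastatin) and control (placebo) groups". It adds that "clinical trial outcomes should not be “change from baseline”, but rather the raw score of an outcome, adjusted for the baseline value". Multiple linear regression is held back for the case that an important baseline characteristic differs between groups.
- **Hypothesis, in Outcomes measures:** "We hypothesize that higher osmolality values will be observed compared to baseline in patients randomized to atorvastatin".
- **Entry criterion, Table 1:** "Diagnosed with NDI, defined by routine 10 h water restriction urine osmolality < 600 mOsm/Kg". This is the same test as the outcome.
- **Table 2:** UOsm is ticked at screening and again at baseline, 4 weeks and 12 weeks.

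**The concern.** A trial should have one primary outcome, and its hypothesis should be the statement that the primary test examines. Here one section names as primary a quantity that another section says a trial should not use. The hypothesis concerns one arm before and after treatment, while the design and the analysis compare two arms.

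Two things are at stake. First, with the t-test as named, the analyst could report either a comparison of change or a comparison of 12-week values as the primary result and cite the article for both. Second, the stated hypothesis could be declared met by any rise on atorvastatin, including one that placebo patients share. Because patients are selected for a low value of the outcome itself, regression to the mean has to be considered as a source of such a rise.

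**Working it through.** **1. Do the two outcome forms lead to different results?**

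Write B for baseline and Y for the 12-week value, with arms A (atorvastatin) and P (placebo).

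- Difference in change = (Y_A − Y_P) − (B_A − B_P). It departs from the raw difference by the chance baseline difference. With 60 patients randomised 1:1 (30 per arm), that difference has standard error SD × √(2/30) = 0.258 SD, where SD is the baseline SD among enrolled patients.
- With equal variances at both visits and correlation r among enrolled patients, SE(change) / SE(raw) = √(2(1 − r)), and SE(ANCOVA) / SE(raw) is about √(1 − r²).

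| r | change / raw | ANCOVA / raw |
|---|---|---|
| 0.3 | √1.4 = 1.18 | √0.91 = 0.95 |
| 0.5 | √1.0 = 1.00 | √0.75 = 0.87 |
| 0.7 | √0.6 = 0.77 | √0.51 = 0.71 |

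So the t-test versions differ in estimate, and in precision except at r = 0.5. In a linear model with baseline as covariate, change and raw value give the same treatment estimate and p-value, and the conflict would not matter. The named t-test does not have that covariate.

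**2. Does the sample size section settle which form is meant?**

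It does not. It uses repeated measures ANOVA with 60 completers, effect size 0.34, two-sided alpha 0.05 and power 0.80. That figure comes out only as Cohen's f for the between-groups factor with a correlation the article does not give: power 0.802 with two measurements at 0.7, or 0.794 with three at 0.8. A single-time-point comparison at f = 0.34 (d = 0.68) has power 0.736. The number of measurements is not stated. Nothing below depends on this figure.

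**3. Could a rise occur in the atorvastatin arm with no drug effect?**

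Input from the article: the 600 mOsm/kg cut lies at about the median of lithium users (50%, Limitations). Assumptions, because the article gives neither: normal distribution, population SD 150-250 mOsm/kg, test-retest correlation ρ 0.5-0.9. Selection below the median puts the qualifying mean 0.399/0.5 = 0.798 SD below the population mean.

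- *Qualifying value used as baseline.* Expected rise = 0.798 × (1 − ρ) × SD. Lowest: 0.798 × 0.1 × 150 = 12. Middle: 0.798 × 0.3 × 200 = 48. Highest: 0.798 × 0.5 × 250 = 100 mOsm/kg.
- *Separate baseline sample, equal correlation between all visits.* Baseline and week 12 have both regressed by the same amount, so the expected rise is 0.
- *Separate baseline sample, correlation falling with each visit (ρ, then ρ²).* Expected rise = 0.798 × ρ(1 − ρ) × SD. Lowest: 0.798 × 0.09 × 150 = 11. Highest: 0.798 × 0.25 × 250 = 50 mOsm/kg.

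Simulation with an inert drug, 30 per arm, 1,500 runs per setting, ρ of 0.5, 0.7 and 0.9:

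| Baseline used | Significant within-arm rise (nominal 2.5%) | Between-arm type I error |
|---|---|---|
| Qualifying value | 14-17% (ρ 0.9), 39-42% (0.7), 62-64% (0.5) | about 5% |
| Separate, equal correlation | 2-3% | about 5% |
| Separate, falling correlation | 12-22% | about 5% |

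Across all settings the between-arm tests (ANCOVA and t-test) gave 4.1-5.9%. That is within simulation error of 5%: the standard error is √(0.05 × 0.95 / 1500) = 0.6 percentage points.

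**The case against.** The strongest reply is that the intended outcome is clear. Three places agree on the baseline-adjusted 12-week value, one of them rejects change scores and says why, and the outlier is an overview sentence that introduces the visit schedule. No section names a week-4 primary analysis. This shows which form should prevail. It does not remove the conflict, because the t-test named alongside does not carry out the adjustment that would make the two forms equivalent.

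On the hypothesis, the reply is that no within-arm test is planned and no within-arm rise is made a success criterion. That stands. A reader might infer from the hypothesis sentence that regression to the mean biases the trial or would make an inert drug look effective. The article does not support that inference. The planned comparison is randomised, placebo-controlled and between arms, regression to the mean affects both arms alike, and the type I error stays at about 5%.

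A reader might also infer that the screening value is the baseline, because the overview counts three visits starting at baseline. Table 2 points the other way, with UOsm ticked in both columns, and Recruitment procedures lets the treating clinician do the qualifying test at a routine visit. The other route there, a later visit with the research assistant, does not exclude overlap, and no sentence says which value is the covariate. The high within-arm percentages therefore belong to an unplanned test under an unconfirmed reading of baseline, with an assumed correlation.

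**Conclusion.** The point holds as an inconsistency in the outcome definition and a mismatch between hypothesis and test. Neither part needs any assumption: change and baseline-adjusted 12-week value are both called primary, the named t-test makes them different analyses, and the hypothesis leaves out placebo.

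Regression to the mean is a conditional illustration of why a within-arm hypothesis is weak. Its size, about 12-100 mOsm/kg, applies only if the qualifying value is the baseline and rests on an assumed SD of 150-250 and reliability of 0.5-0.9. With Table 2's separate baseline sample it is about zero under stable correlation, and about 11-50 mOsm/kg if correlation falls over visits. The randomised between-arm test is not biased in any of these cases. The wording should be corrected because it determines what the trial may claim.

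**What to change.** - **Overview of study procedures:** replace change with 12-week UOsm compared between arms and adjusted for baseline. Describe the week-4 value as supportive.
- **Planned analysis:** name a linear model (ANCOVA) with baseline UOsm as covariate for the primary comparison, in place of the t-test.
- **Outcomes measures:** restate the hypothesis as: mean 12-week UOsm, adjusted for baseline, is higher with atorvastatin than with placebo.
- **Definition of baseline:** state that the covariate is the baseline-visit UOsm, not the screening value that qualified the patient.
- **Interpretation:** state that no efficacy conclusion will be drawn from change within an arm.

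The cost is wording in three sections. No visit, sample or patient is added, since Table 2 already schedules both the screening and the baseline measurement.

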#### Safety and tolerability measures

Safety and tolerability outcome measures will be assessed including blood tests at routine and follow-up visits to ensure patient health (monitoring atorvastatin-related adverse effects). Blood tests will allow the monitoring of serum lithium levels, lipid profile (including LDL levels), creatinine kinase, liver function enzymes, calcium, thyroid stimulating hormone, and electrolytes. Patient reported symptoms – e.g. for myalgias – are also reported. In addition, mood assessments - YMRS, MADRS, QIDS, and AMSRS assessments during follow-up visits will be used to monitor mood changes in patients. YMRS is an eleven-item scale to assess manic symptoms in individuals [27]. MADRS is a ten-item scale for a measure of depressive symptoms [26]. QIDS is a twenty-item self-report measure on depression [28], whereas the ASRMS is a five-item self-report measure for manic symptoms [29].

#### Baseline demographic and clinical characteristics

We collect information on a number of baseline demographic and clinical characteristics, including: age, sex, body mass index (BMI), psychiatric and other medication history including duration of lithium use and dosage. Of these factors, age, lithium-level, duration, dosage and anti-psychotic use have been associated with NDI [17, 30].

#### Planned analysis

We will use independent two-tailed Student’s t-test (or non-parametric equivalent) to compare the primary outcome (raw score values of urinary osmolality at 12-weeks, adjusted for baseline) and secondary outcomes (self-reported fluid intake and variation in aquaporin 2 protein abundance in urinary exosomes at 12-week follow-up, adjusted for baseline) between the treatment (atorvastatin) and control (placebo) groups. The consensus in the statistics RCT literature is that clinical trial outcomes should not be “change from baseline”, but rather the raw score of an outcome, adjusted for the baseline value [37]. Randomization is expected to balance potential confounders between the treatment and placebo groups since both groups are anticipated to have roughly equal baseline characteristics, which we will assess using t-tests (or non-parametric equivalent) and chi-squared tests, as appropriate. However, in the event that any important baseline characteristic differs between groups, we will use multiple linear regression to control for that particular characteristic.

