#### Sample size justification

On repeated measures ANOVA, 60 study completers will allow us to observe an effect size of 0.34 at two-tailed alpha = 0.05 and Power (1-Beta) =0.8 [38]. In our previous cross-sectional findings in chronic lithium users, the effect size of statins on NDI was 0.33 [21], however that was not an intervention study. We acknowledge that there is relatively little data at the current time to justify the sample size. This RCT will provide the necessary and adequate data to plan a subsequent larger RCT [39].

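### The primary test named (a two-sample t-test or rank equivalent) has no covariate, so it cannot give the baseline-adjusted 12-week comparison that the protocol promises

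*Protocol article*

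**What the plan says.** - **Planned analysis (test).** An independent two-tailed Student's "t-test (or non-parametric equivalent) to compare the primary outcome (raw score values of urinary osmolality at 12-weeks, adjusted for baseline". The same sentence applies this test to the secondary outcomes, fluid intake and aquaporin 2.
- **Planned analysis (principle).** The authors state that "clinical trial outcomes should not be “change from baseline”, but rather the raw score of an outcome, adjusted for the baseline value".
- **Outcomes measures.** "We will assess the raw urine osmolality value at 12-weeks, adjusted for baseline". The Abstract (Methods) makes the same commitment.
- **Planned analysis (regression).** The only model able to carry a covariate is conditional: "in the event that any important baseline characteristic differs between groups, we will use multiple linear regression to control for that particular characteristic". Differences are to be assessed with t-tests (or non-parametric equivalents) and chi-squared tests.
- **Overview of study procedures.** The outcome is described differently: "The primary outcome is change in 10 h water restriction urine osmolality (mOsm/kg", assessed at baseline, 4 weeks and 12 weeks.
- **Sample size justification.** A third model appears: "On repeated measures ANOVA, 60 study completers will allow us to observe an effect size of 0.34" "at two-tailed alpha = 0.05 and Power (1-Beta) =0.8".

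The article nowhere names ANCOVA, or regression on baseline osmolality, as the unconditional primary analysis.

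**The concern.** The outcome definition and the test sit in one sentence and do not fit together. A two-sample t-test or rank-sum test compares two columns of numbers and has no place for a baseline value. Run on raw 12-week values, it ignores baseline. Run on differences, it is the change-score analysis that the paragraph rejects.

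The conditional regression does not fill the gap. The promised adjustment is unconditional, whereas this one switches on only after the arms have been compared at baseline and a difference has been judged important, a word the article does not define. The primary model then depends on the data, and a baseline imbalance too small to trigger the rule stays in the estimate.

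At stake are the precision of the treatment effect in a 60-patient trial meant to inform a larger one, and a primary analysis that is fixed before the data are seen.

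**Working it through.** **1. Which reading satisfies both halves of the sentence?**

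| Reading | Is it the named test? | Does it give the promised adjustment? |
|---|---|---|
| t-test on raw 12-week values | yes | no |
| t-test on change scores | yes | no; rejected in the same paragraph |
| t-test on residuals from a regression on baseline | only after a regression step | yes, but the step is not in the article |
| regression triggered by observed imbalance | no | only when triggered |

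None satisfies both as written.

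**2. The protocol's own figure.** Inputs from Sample size justification: N = 60, two-tailed alpha 0.05, power 0.80, effect size 0.34. The metric, the number of measurements m and the within-patient correlation ρ are not given, so 0.34 cannot be derived from the stated inputs alone. For the between-group effect in a repeated measures ANOVA, λ = f²·N·m / (1 + (m − 1)ρ) on 1 and 58 df:
- m = 2, ρ = 0.7: λ = 0.34² × 60 × 2 / 1.7 = 8.16, power 80.2%.
- m = 3, ρ = 0.75: power 81.0%. With ρ = 0.8: 79.4%.
- ρ = 0.5: the detectable f is 0.319 (m = 2) or 0.300 (m = 3).

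So 0.34 is attainable as Cohen's f under an undeclared correlation and is not shown to be wrong. It belongs, however, to a model other than the named test.

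**3. Power of the named test.** Allocation is 1:1, so there are 30 per arm if 60 complete. For two equal groups d = 2f = 0.68. The noncentrality is d·√(30/2) = 0.68 × √15 = 2.634. On 58 df (critical value 2.002) power is 73.6%, whatever r is, because the test does not use baseline. Its smallest detectable difference at 80% power is d = 0.736 (f = 0.368).

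**4. Power with the baseline covariate.** ANCOVA multiplies the residual variance by 1 − r². The noncentrality is d·√15 / √(1 − r²) × √(57/58), on 57 df; the last factor is a small allowance for chance baseline imbalance. The correlation r is assumed.

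| r | √(1 − r²) | ANCOVA, d = 0.68 | ANCOVA, d = 0.34 |
|---|---|---|---|
| 0 | 1.000 | 72.8% | 24.9% |
| 0.3 | 0.954 | 76.7% | 26.9% |
| 0.5 | 0.866 | 84.2% | 31.6% |
| 0.7 | 0.714 | 94.9% | 43.5% |
| *Raw t-test, any r* | | *73.6%* | *25.4%* |

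Without the small allowance and the lost degree of freedom, the d = 0.68 values at r = 0.5 and 0.7 are 84.9% and 95.2%. The d = 0.34 column applies if the stated effect size is Cohen's d. The second column is also the approximate ratio of the two standard errors.

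**5. Simulation check** (20,000 trials per setting, d = 0.68). At r = 0.5 the raw t-test had 73.0% power, ANCOVA 83.9% and the t-test on residuals 83.8%. At r = 0.7 the figures were 73.7%, 94.9% and 94.9%. With no treatment effect, all three rejected in 5.0% to 5.2% of trials.

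**The case against.** The best defence is that the intention is plain. The adjusted 12-week value is promised in three places and change scores are rejected, so the test label may simply be loose. A t-test on residualised values would perform almost exactly like ANCOVA, and the ANCOVA treatment effect is itself tested with a t statistic. The article is also a condensation, and an independent statistician will run the analysis. What stands is that an analyst who honours the adjustment loses nothing. But that analyst must add a regression step that the article does not state. The article does not leave the test to another document; it names one that conflicts with its own outcome definition.

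Three stronger inferences a reader might draw are not supported:

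- **That the literal analysis is invalid.** Under randomisation the unadjusted t-test keeps its type I error. The loss is of precision and of a fixed primary model.
- **That every chance baseline imbalance would be left in the estimate.** The conditional regression would presumably deal with a conspicuous one. Smaller ones remain.
- **That the trial certainly loses 10 to 20 points of power.** That needs 0.34 to be Cohen's f and r between 0.5 and 0.7. The article states neither. Entry is restricted to osmolality below 600 mOsm/kg, and such truncation tends to lower r. At r = 0 there is no gain.

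**Conclusion.** The contradiction is established from the text and needs no assumption: the named test cannot produce the promised baseline-adjusted comparison, and the only covariate model is conditional on observed imbalance. The same holds for fluid intake and aquaporin 2.

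The cost of following the plan literally is uncertain. If 0.34 is Cohen's f, it runs from nothing at r = 0 to about 21 percentage points at r = 0.7 (94.9 − 73.6 = 21.3). If 0.34 is Cohen's d, it runs from nothing to about 18 points (43.5 − 25.4 = 18.1), and power is low under either analysis. All these figures assume 60 completers, 30 per arm, normal errors and equal variances. They show the scale of the loss and do not predict it for this trial.

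**What to change.** 1. In Planned analysis, name linear regression (ANCOVA) of 12-week urine osmolality on treatment, with baseline osmolality as covariate, as the primary analysis regardless of observed imbalance. Report the adjusted mean difference with its 95% confidence interval.
2. Preferably include the stratification factors, diagnosis and site, in the same model.
3. Use this model for fluid intake and aquaporin 2.
4. Replace the non-parametric alternative with one named fallback that keeps the covariate, for example rank-based ANCOVA.
5. Reconcile Overview of study procedures, which calls the outcome a change, and Sample size justification, which uses repeated measures ANOVA, with this analysis. State the metric of 0.34 and the correlation assumed.

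The cost is a few sentences. Baseline osmolality is already collected, so no extra visit, sample or patient is needed.

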### Randomization and concealment

After eligibility is confirmed and patients have given consent, patients will be randomized in a 1:1 ratio to receive either 20 mg per day of atorvastatin (treatment group) or placebo (control group). We are using a stratified randomization, with two strata: 1. Diagnosis (bipolar disorder, other diagnosis (e.g. depression, schizoaffective disorder), and 2. McGill hospital site (Douglas Mental Health Institute, Jewish General Hospital (JGH), and McGill University Health Centre (MUHC)). An independent entity, the Lady Davis Institute Data Management Unit is responsible for setting up data management software (Redcap) and randomization. Allocation of participants to groups is concealed in an envelope that only the pharmacy at the Douglas Institute has access to. The patients, clinicians, researcher and outcome assessors will all be blind to the treatment allocation. An independent statistician will perform the statistical analyses.

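### Covariates enter the primary analysis only if a baseline comparison between arms shows a difference, so the primary model depends on chance imbalance and an undefined judgement instead of being fixed by prognosis

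*Protocol article*

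**What the plan says.** All references are to the protocol article.

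- **Planned analysis** names a two-sample t-test, or a non-parametric equivalent, for the primary outcome, described as "raw score values of urinary osmolality at 12-weeks, adjusted for baseline". Adjustment for baseline osmolality is stated without condition, here and under Outcomes measures.
- The same section expects randomisation to balance the arms, "which we will assess using t-tests (or non-parametric equivalent) and chi-squared tests, as appropriate".
- It then gives the rule at issue: "in the event that any important baseline characteristic differs between groups, we will use multiple linear regression to control for that particular characteristic". It does not define *important* or *differs*, and it does not call the regression secondary or a sensitivity analysis.
- **Baseline demographic and clinical characteristics** lists what is collected and adds: "Of these factors, age, lithium-level, duration, dosage and anti-psychotic use have been associated with NDI". None of these factors is fixed in the model.
- **Randomization and concealment** stratifies by diagnosis and hospital site. Neither factor appears in the planned analysis.

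**The concern.** After proper randomisation, any baseline difference between arms is due to chance, so a significance test of it examines a null hypothesis already known to be true. The result says nothing about whether the variable predicts 12-week osmolality, and prediction is the reason to adjust. A strong predictor that happens to be balanced is left out, and an irrelevant variable that happens to be unbalanced goes in.

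Two things are at stake. First, the primary analysis is not one analysis: it depends on baseline tests and on what someone later considers important, so two careful analysts could report different primary p-values from the same data. Second, precision is given up whenever a useful covariate stays out because it was balanced.

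**Working it through.** **Inputs from the article.** 60 completers, allocated 1:1, so 30 per arm; "two-tailed alpha = 0.05 and Power (1-Beta) =0.8"; baseline osmolality always adjusted for; five factors named as associated with NDI.

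**Assumed, because the article gives no figure.** A 5% threshold for each baseline test, independent characteristics, the baseline-to-12-week correlation r, the prognostic strength of the covariates, and the true effect.

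**Step 1. The plan's own figure, used to choose a true effect.** The article says that "60 study completers will allow us to observe an effect size of 0.34" on repeated measures ANOVA, without naming the metric. Read as Cohen's f for the between-group effect, the noncentrality is λ = f²·N·m / (1 + (m − 1)ρ), with 1 and 58 degrees of freedom. With m = 2 measurements and ρ = 0.7 (neither is stated), λ = 0.34² × 60 × 2 / 1.7 = 8.16. Power is 80.2%, so 0.34 is reproduced under those values. For two groups d = 2f = 0.68, which is the effect used in Step 3.

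**Step 2. How often chance alone changes the model.** P(at least one p < 0.05) = 1 − 0.95^k.

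| Characteristics tested, k | Chance the model changes |
|---|---|
| 5 (the named NDI factors) | 1 − 0.774 = 22.6% |
| 8 | 1 − 0.663 = 33.7% |
| 12 | 1 − 0.540 = 46.0% |

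**Step 3. Effect on error rate and power with baseline osmolality always in.** Simulation with 30 per arm, d = 0.68, nine other candidate covariates of which one has effect 0.3 and the rest none, 6,000 runs. The short fixed model holds baseline, the prognostic covariate and one useless covariate.

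| r | Rule: type I error | Rule: power | Baseline-only ANCOVA: power | Short fixed model: power |
|---|---|---|---|---|
| 0.5 | 4.8% | 83% | 84% | 87% |
| 0.7 | 4.8% | 94% | 95% | 97% |

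The rule loses 1 point against baseline-only ANCOVA and 87 − 83 = 4 or 97 − 94 = 3 points against the short fixed model. A repeat gave type I error of 4.3–5.2%, and power of 83–95% for the rule against 85–97% for the short fixed model. The Monte Carlo standard error of a 5% rate at 6,000 runs is √(0.05 × 0.95 / 6,000) = 0.28 points.

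**Step 4. Sensitivity to prognostic strength.** 30 per arm, r = 0.5, true effect 0.6 SD, 20,000 runs. R² is the share of outcome variance explained by the covariates in addition to baseline. The fixed model holds all of them.

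| Covariates | R² | Type I error, rule / fixed | Power, rule / fixed |
|---|---|---|---|
| 1 | 0.2 | 4.1% / 4.8% | 75.3% / 85.6% |
| 1 | 0.4 | 3.5% / 5.0% | 76.4% / 96.7% |
| 6 | 0 | 5.0% / 4.9% | 73.1% / 69.6% |
| 6 | 0.2 | 4.4% / 5.2% | 74.7% / 82.6% |
| 6 | 0.4 | 3.7% / 5.0% | 75.6% / 95.2% |

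**Why the rule errs on the conservative side.** Take one covariate with R² = 0.2. In the 5.0% of trials where it is unbalanced, the model without it rejects 18.9% of the time under the null, and adjustment brings this to 4.2%. The other trials contribute 4.81% − 0.05 × 18.9% = 3.86%. The total is 3.86% + 0.05 × 4.2% = 4.07%. The rule removes the false positives from unbalanced trials and leaves the rest analysed with more residual variance than necessary.

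**Step 5. Choosing between results.** If the analyst reports whichever of the unadjusted-for-covariates and rule-based results is significant, type I error in the Step 4 runs (including one covariate at R² = 0) is 4.9–5.6%. A freer choice among covariate sets was not calculated.

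**The case against.** - **The error rate is not inflated.** A reader might infer that data-dependent adjustment pushes type I error above 5%. Steps 3 and 4 do not support that: used mechanically, the rule is near nominal or slightly conservative. Even picking the better of two results moves it only to 4.9–5.6%. This objection stands.
- **The power loss is modest if baseline is in.** A reader might take the rule to cover baseline osmolality as well and compare 73% power with 85% or 95% for baseline-adjusted ANCOVA, a gap of 12 to 22 points. The article does not support that reading, because it states baseline adjustment without condition. A plain t-test cannot make that adjustment, but this is a separate point about the named test and not a cost of selecting covariates by imbalance. This objection also stands.
- **Prognostic strength is unknown.** The article says only that five factors have been associated with NDI, not how well they predict 12-week osmolality given baseline. The larger losses in Step 4 need R² of 0.2–0.4, and at R² = 0 a fixed six-covariate model does worse than the rule. This limits the size of the claim and argues for a short list.
- **The trigger may be narrower.** Only *important* characteristics count, so 34–46% is high if the list is the five named factors; 23% is then the figure.
- **The article is condensed and the trial preliminary.** A fuller document might define the terms. It would not cure the rule the article states, which selects by imbalance. That the trial is meant to inform a larger one lowers the stakes but does not remove them.

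**Conclusion.** The point holds as a defect in how the primary model is chosen. The article states a rule under which baseline tests of randomised data, plus an undefined judgement of importance, decide which covariates enter the primary comparison. Chance alone would change the model in about 23% of trials with five candidates, assuming independent tests at 5%.

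The numerical harm under mechanical use is small: type I error of about 4.3–5.2%, and power about 1–4 points below a short fixed model. This assumes 30 per arm, d = 0.68, a baseline correlation of 0.5–0.7, modest covariate effects, and baseline osmolality always in the model. Strongly prognostic covariates (R² 0.2–0.4) would raise the power loss to about 8–20 points, but the article gives no evidence for that strength. The main weakness is that the undefined terms leave room for selective adjustment of the primary result. The rule should be changed, but it does not invalidate the trial.

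**What to change.** In Planned analysis, delete the between-arm baseline significance tests and the conditional regression. State one primary linear model in advance: 12-week urine osmolality on treatment, baseline osmolality, diagnosis and site, plus at most one or two predictors named now from the five the article lists, for example age and duration of lithium use. Use the same approach for the secondary outcomes. Report baseline characteristics by arm descriptively, without p-values. Label any further adjustment as a sensitivity analysis.

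The cost is wording and a few degrees of freedom. With two diagnosis groups, three sites and two predictors, the model has 1 + 1 + 1 + 1 + 2 + 2 = 8 parameters, leaving 60 − 8 = 52 residual degrees of freedom against 57 for baseline-only adjustment. If an added predictor has no prognostic value, the loss is small: for one useless covariate in the Step 4 setting, power was 73.5% for the fixed model against 74.2% for the rule. The 3.5-point loss with six useless covariates (73.1% to 69.6%) is the reason to keep the list short.
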